# Protocol Bovine Intervention Trial

PARTICIPATING SITE(S)

National Institute of Parasitic Diseases, China, CDC

Queensland Institute of Medical Research, Australia

School of Population Health, The University of Queensland, Australia

STUDY MANAGEMENT

All questions concerning this protocol should be sent via email to [name] [contact]

SCHEMA

It has been hypothesized that bovine, especially buffalo, infections are responsible for the persistence of human schistosomiasis transmission in the lake and marshland areas of China. A TMRC/NIH-supported pilot intervention study in the Poyang Lake region in the Jiangxi Province concluded in 2003 and the results are supportive of this hypothesis. The bovine intervention trial aims to: 1) Repeat the results obtained from the TMRC/NIH-supported pilot intervention study. However on a larger and more generalizable scale

; 2) Examine the efficacy of bovine chemotherapy on human infection and reinfection rates; 3) Assess bovine chemotherapy as a plausible schistosomiasis control method;

4) Integrate the intervention into the earlier TMRC developed mathematical model. The study will be conducted over a maximum of 4 years, with an interim analysis after 2 years within pairs of villages.

TITLE: A bovine intervention trial

COUNTRY: China

DURATION TO COMPLETION: 2006-2008

DESIGN: Cluster-randomized design with a longitudinal study of a sentinel cohort

SAMPLE SIZE: A sample size consisting of at least 300 residents per village will constitute the sentinel cohort; all bovines will be sampled in all pairs of villages at baseline and in the intervention villages during the trial.

POPULATION: The population will be from the pairs of selected administrative villages in Hunan and Jiangxi provinces in P.R. China

REGIMEN: The study is an intervention study. It will entail an initial treatment with Praziquantel of humans in all villages and bovines within the intervention villages only. Humans will be mass treated annually just after the transmission season and Bovines will be mass treated twice annually, just before and after transmission season. Prior to the annual mass treatment, identification of infected persons in the selected cohort, via standard stool examination (Kato-Katz method) will be undertaken. A name list of positives will be provided to the local control program and will be treated by local control teams according to standard protocols established within the schistosomiasis control program in China. This is necessary for ethical reasons.

# Introduction

**1.1 Background**

600 million Chinese have parasitic infections. One of the most important, from the public health and clinical perspective, is schistosomiasis (Hotez et al., 1997). Schistosomiasis japonica is a serious disease, typified by long-term chronicity, and a major disease risk for more than 40 million people living in the tropical and sub-tropical zones of China (Chen and Feng, 1999). The disease disabled and killed millions of Chinese peasants before systematic control programs began in the 1950s (Chen, 1999). Infection remains a major public health concern despite the 45 years of extraordinary historic emphasis and intensive efforts at controlling this disease. Even today, it is estimated that over 1 million people and several hundred thousand livestock, including 100,250 bovines, are infected (Ross et al., 2001). The major endemic foci are in the marsh and lake regions (Dongting and Poyang Lakes; **Figure 1**) of Southern China, which cover a vast area of five provinces, Jiangsu, Anhui, Hubei, Jiangxi and Hunan. Since 1985, the rural Chinese economy has been boosted (resulting in an improved standard of living) but the prevalence of *S. japonicum* and its associated morbidity have also risen in focus areas (Yuan, 1992). Unlike the other schistosome species known to infect man, the oriental schistosome, *Schistosoma japonicum*, is zoonotic, with a range of mammalian reservoirs that complicates control efforts. Schistosome infection debilitates domestic livestock that are used for food and as work animals in Southern China. This adds to the economic burden and suffering of communities in the *S. japonicum*-endemic areas.

[figure not shown]

**Figure 1. Map of Southern China showing the position of the Three Gorges Dam and Poyang and Dongting Lakes on the River Yangtze**.

Clinical features of schistosomiasis japonica are severe, ranging from fever, headache and lethargy, to serious fibro-obstructive pathology leading to portal hypertension, ascites and hepatosplenomegaly, which can cause premature death (Ross et al., 2002). As well, infected children are stunted and have cognitive defects impairing memory and learning ability. The onset of advanced schistosomiasis poses a particular public health and socio-economic problem. There are over 30,000 cases of advanced disease with 8,000 new cases reported annually. The onset of advanced disease promotes the most serious clinical manifestations and it is difficult to provide adequate treatment for affected patients, many of whom die resulting in severe consequences both for the patient’s family and the community as a whole. Current control is based on community chemotherapy with a single dose of praziquantel. Vaccines (for use in bovine and humans) in combination with other control strategies, including the use of new drugs, are needed to make elimination of the disease possible (Todd & Colley, 2002). New approaches, advocated by the Chinese Government and other organizations including WHO, are required to supplement current control strategies that are difficult and costly (Guyatt, 1998). We recently brought together the results of control technology advances, including the success of recent World Bank inputs, to mathematically model prospects for the future control of schistosomiasis in China (Williams et al., 2002). The model shows that an integrated approach to control can successfully lead to eradication of infection.

China is in the midst of major environmental and social change and a further important issue concerns construction of the giant Three Gorges Dam **(Figure 1)** across the Yangtze (Chang Jiang) River, whose drainage provides the great corridor of parasitic disease in China. Due to be filled by 2009, the dam, which was recently closed, and the 600 km long reservoir it will create, will have a global environmental impact on the transmission and geographical distribution of schistosomiasis both above and below the dam (Zheng et al., 2002). The Ministry of Health in China is currently investigating the increased risk for schistosomiasis associated with the dam. No absolute schistosomiasis data exist to indicate the probable outcomes but there is no doubt the dam will change the Yangtze basin ecology significantly. A second wave of problems has been caused by a plague of recent floods that have devastated numerous regions of the Yangtze River drainage. The recent flood problems are associated with increasing deforestation in the mountains coupled with reclaiming of lakes and marshy lowlands in the Lake Districts in the lower Yangtze drainage. This will increase snail habitats and, consequently, the risk of schistosome transmission. Over the coming years the numbers of oncomelanid-snail breeding areas will be increased substantially and schistosomiasis transmission will intensify. As a result we predict a marked elevation in infection rates and associated morbidity that will impact significantly on control.

## 1.2 Rationale

Bovines (cattle and water buffalo) are the major reservoir of *S. japonicum* within the marsh and lake regions of China. A TMRC-supported pilot intervention study (1998-2003) around the Poyang Lake, Jiangxi Province aimed at providing proof-of principle for the hypothesis that bovine, especially buffalo, infections are responsible for the persistence of human schistosomiasis transmission in the marshlands and lake areas of China. The work has major implications for future integrated schistosomiasis control including the use of chemotherapy for bovines and it underpins the rationale for development and implementation of a veterinary-based vaccine for use in reservoir hosts, particularly buffaloes. This pilot study (1998-2003) was comparing human infection incidence in an intervention village (Jishan) (in which bovines were treated) and a control village (Hexi) (no bovine treatment) (Guo et al., 2001; Davis et al., 2002). We found that the incidences of infection in residents and bovines were reduced significantly in the intervention village. We used the predicted human infection incidence data in our mathematical model (Williams et al, 2002) based on data collected in Jishan village to compare predicted prevented infections associated with bovine treatment (**Figure 2**).

[figure not shown]
**Figure 2.** **Predicted human infection prevalence from the mathematical model, based on data collected in Jishan village, for human treatment only (broken line) and human and bovine treatment combined (solid line). Solid dots show the prevalences actually observed in Jishan. The gap between the two curves represents predicted prevented infections associated with bovine treatment.**

***Aim:*** The pilot study provides proof of principle but we wish now to undertake a more stringent bovine intervention trial (2004-2008) using a cluster-randomized design, with increased power and general application.

### 1.3 Study Design

**Cluster Randomized Design:** We will select pairs of villages from identified communities (human prevalence 10-15%; bovine prevalence 10-15%) in Jiangxi province and Hunan province, with pairs being matched as closely as possible on factors related to transmission: i.e. infection levels, transmission ecology (e.g.: water height, flooding patterns), and force of infection (e.g.: water contact patterns, buffalo: human numbers, sanitation practices, herding practices). The trial will aim to select the villages that provide closest matching in pairs. Within each pair, one village will be randomly chosen as intervention (bovines treated twice annually) and the other will be a control. Annual mass treatment of residents will be carried out in both villages. The end-point for the trial will be human infection rates. The efficacy of bovine treatment will be measured by the accumulated comparison of human infection rates across intervention and control villages, and will be reflected in the predicted percentage of human infection-years prevented by the intervention. Human infection rates will be assessed at the end of each year for 4 years.

### 2.0 Study Objectives

This study aims to achieve the following objectives.

1. Repeat the results obtained from the TMRC-supported pilot intervention study, regarding the hypothesis that “Bovine, especially buffalo, infections are responsible for the persistence of human schistosomiasis transmission in the marshlands and lake areas of China.” However on a larger and more generalizable scale.
2. Examine the efficacy of bovine chemotherapy on human infection and reinfection rates and how this gives insight into the use of a potential bovine vaccine.
3. Assess bovine chemotherapy as a plausible schistosomiasis control method, particularly in combination with human treatment.
4. Integrate the empirical data collected from the study into the previously TMRC-developed mathematical model.
5. **Study Procedure**

**3.1 Study procedure**

##### Pre-Trial

A research team in each province will be established in order to carry out the fieldwork and the laboratory testing in their respective research institutes.

A sampling survey in Jiangxi Province will be done by early September 2004. The data from this survey will be distributed to the project investigators for the selection of the study villages.

Approximately 40-50 human faecal samples and 30 bovine faecal samples per village will be collected. Additionally, during the sampling survey, faecal examinations for sheep and goats (40-50 each species, hatching method) will be carried out to estimate their prevalence, as a variable for modelling.

Maps of the study sites will be prepared in order to show their location.

After the Jiangxi sampling survey, the study villages will be selected and matched according to the village selection criteria, by the project investigators. Within each pair, one village will be randomly selected as the intervention village thus leaving the other of the pair as the control.

A current list (census) of each village population by household will be constructed prior to baseline

**Stage 1:** October 2004

##### Baseline Survey

##### Humans

This will include a questionnaire-based interview whereby demographic information (including name, sex, date of birth, length of time resident in the village), water contact information, and a brief medical history (schistosomiasis) will be obtained. Each person will be assigned a personal identification number (PID) and entered into a case report form (CRF). Their PID will be kept for the duration of the study.

All village residents will receive 2 plastic containers for fecal samples. Containers will be labeled with PID, and the date of distribution. Participants will be instructed to deposit samples from their own faeces, separated by at most three days, into each container and to return the container immediately to one of several collection points, where the sample will be stored at 4 °C. Fecal samples returned later than 48 hours after defecation will not be accepted and new containers will be issued. Slide preparation (three slides per stool specimen) will occur 24 hours after receipt of stool sample using the Kato-Katz thick smear technique (Katz et al 1972). These samples will provide the baseline prevalence and intensity of infection within each village.

Anyone found to be egg positive would be treated for ethical reasons.

##### Bovines

A baseline survey will also be carried out on the bovines within the villages. A stool sample will be obtained from all bovines and tested, using thetraditional Chinese miracidial hatching test in order to determine the baseline prevalence and intensity of infection within each village. Sheep and goats will also be examined at baseline

Permission will be obtained from the bovine owners to allow us to treat their bovines. Note this will only happen in the intervention villages.

Note: All Bovines will be examined and treated in the intervention villages; they will only be examined in the control villages.

##### Snails

Want to measure the prevalence of infection in snails and the density of infected snails per unit area. To do this we need to conduct random quadrat sampling (1000 frames 20-50m per frame) (Chinese method) of the marshland areas relevant to each village. Use GPS machine, to identify the area that was surveyed.

This will need to be done at baseline, early October.

Note: Snail surveys will also be done and in March/April each year.

##### Sentinel cohort selection

Within each village a sentinel cohort will be selected and followed up on for a maximum of 4 years. This cohort will be selected by the following procedure:

The cohort will be selected for the study based on the inclusion criteria. The project’s principal investigators will perform the selection. The sentinel cohort will comprise at least 300 residents per village.

The research team will then visit the households of those selected in order to recruit them for the study and to obtain informed consent from individual participating adults and assent for minors. The subject (or parent or legal guardian if the subject is less than eighteen years of age) will be asked to read and sign an informed consent approved by the IRB. Their personal identification number (PID) from the baseline survey will be entered on their consent form prior to its signing. It must be noted that at the start of the study there must be a minimum of 300 residents in each cohort.

**Stage 2:** November 2004

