##### Outcome Measures

Humans:

Sentinel cohort members will receive 2 plastic containers for fecal samples. Containers will be labeled with PID, and the date of distribution. Participants will be instructed to deposit samples from their own faeces, separated by at most three days, into each container and to return the container immediately to one of several collection points, where the sample will be stored at 4 °C. Fecal samples returned later than 48 hours after defecation will not be accepted and new containers will be issued. Slide preparation (three slides per stool specimen) will occur 24 hours after receipt of stool sample using the Kato-Katz thick smear technique (Katz et al 1972). These samples will provide the outcome measures for each village 1 year after baseline. Water contact data will also be collected for that month via the completion of a questionnaire

Cohort members found to be egg positive will be treated for ethical reasons.

Water contact questionnaire survey

The questionnaire will be conducted once a year after transmission season (October-November) by trained team members, no more than 3 team members will be responsible for the survey for one village during the entire project period. The content of the water contact survey is listed in the questionnaire form. Each item must be answered with no blank.

Bovines:

A stool sample from every bovine will be collected and tested using the traditional Chinese MHT, These samples will provide the outcome measures for each village 1 year after baseline.

**Stage 5:** November 2005

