### 4.2 Cohort Selection

# Cohort Inclusion Criteria

1. Resident of the administrative village and/or natural village selected for study.
2. Has been a resident of the village for >12 months.
3. 5-60 years of age.
4. Will not be migrating in the next 4 years.
5. Those who continuously reside in the study area over the study period*.
6. The resident has given informed consent.
7. Minors have the informed consent of their parent/guardian.

* Residents who are in the study area only weekends or once a month (such as students) are assumed not to have the same kind or an equal amount of exposure as individuals continuously resident in the study area. Inclusion of such individuals would contribute to either an overestimation or underestimation of prevalence.

Out-migration (dates and reasons) will be recorded for cohort members. Owing to the close familial relationships within the village, reporting of out-migrants will rely on family members or neighbours.

In addition, in-migrants to the area, intending to become longer-term residents will be documented, but not included in the cohort. Thus, the study will have documentation of the village population, within which the cohort is embedded.

NOTE: The sentinel cohort in each village must have at least 300 members

1. **Clinical Considerations**

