**7.3 Statistical significance, Generalizability and Power**

In order for this study to yield results that are statistically significant and are able to be applied to a population (i.e. generalizable), there needs to be adequate power and a sample size providing an accurate representation of the affected community. It has been determined that for generalizability and statistical significance, a minimum of 4 village pairs is required, with a sample size of 300 per village, with a village population of approximately 1000.

The following table shows the power calculations based on the above minimum considerations. The

table also shows these powers with varying degrees of the bovine effect on the village and the

percentage of the bovines that are actually treated.

Assumptions

- Design effect is 1.5, in other words the actual sample size is reduced by a factor of 1.5 to give an effective sample size. This reduction is due to the extra similarity within clusters that means the observations cannot be treated as independent.
- Assume an attrition rate between years 1 and 2 of 20%.
- Assume that years 1 and 2 are independent for the cumulative power.
- Target (net) sample size is the number obtained in each village for testing (after excluding non-compliers).
- Use a significance level of 1% year 1 and 5% year 2.
- This study works on treating the whole village.
- Assume a village size of 1000.

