# Table of sample size (no new villages)

| Bovine effect size &  % Bovines treated | # Paired villages | Target sample size per village | Power %  (Year 1) | Power %  (Year 2) | Cumulative power  (Yrs 1 & 2) |
| --- | --- | --- | --- | --- | --- |
| 60% & 70% | 4 | 300 | 26.7 | 80.3 | 89.5 |
| 60% & 80% | 4 | 300 | 38.1 | 88.7 | 95.7 |
| 60% & 90% | 4 | 300 | 51.3 | 94 | 98.5 |
|  |  |  |  |  |  |
| 70% & 70% | 4 | 300 | 38.2 | 90.1 | 96.2 |
| 70% & 80% | 4 | 300 | 53.3 | 95.5 | 98.9 |
| 70% & 90% | 4 | 300 | 68.6 | 98 | 99.8 |
|  |  |  |  |  |  |
| 80% & 70% | 4 | 300 | 50.9 | 95.7 | 98.9 |
| 80% & 80% | 4 | 300 | 68.0 | 98.4 | 99.8 |
| 80% & 90 % | 4 | 300 | 82.7 | 99.4 | 100 |

Target sample size per village corresponds to the number of villagers sampled (not necessarily all those exposed). Powers are based on adjusting the sample size per village for attrition and a design effect.

- 1. **Analysis Plan**

Initial descriptive statistics will be performed to examine an overall trend in the data. This will be followed by the calculation of the outcome measures. These outcome measures will then be compared across control and intervention villages in order to determine the efficacy of the intervention. The empirical data gathered in this study will be put into the previously developed mathematical model (Williams *et al* 2002) in order to validate its predictions. Microsoft Access will be used for Data Management and SAS will be used for Data Analysis.

1. **Ethics**

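### The power table assumes 300 people tested per village in Year 1, but the protocol secures only 300 enrolled a year earlier, so the tabulated powers are not secured at the stated minimum

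*Protocol*

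**What the plan says.** **Power basis.** Section 7.3 says that "a minimum of 4 village pairs is required, with a sample size of 300 per village". It then defines what the 300 counts: "Target (net) sample size is the number obtained in each village for testing (after excluding non-compliers". The only attrition rate it gives is this one: "Assume an attrition rate between years 1 and 2 of 20" per cent. The note under the power table adds that "Powers are based on adjusting the sample size per village for attrition and a design effect" and names no further rate.

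**Enrolment rule.** Section 3.1 (Stage 1, October 2004, sentinel cohort selection) requires that "at the start of the study there must be a minimum of 300 residents in each cohort". Section 4.2 repeats it: "The sentinel cohort in each village must have at least 300 members". The sample-size line of the schema gives the same minimum. No larger enrolment target appears.

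**Timing.** The first outcome stools are collected in Stage 4, October-November 2005: "These samples will provide the outcome measures for each village 1 year after baseline".

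**Closed cohort.** Under Sections 4.2 and 6.1, people who move into the village are documented but do not join the cohort.

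**The concern.** The same figure, 300, is used for two different quantities: a net count of people tested in Year 1 in the power calculation, and a gross count of people enrolled in the recruitment rule. Twelve months separate them, and no stated allowance covers that interval.

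The protocol itself expects losses of this kind. Section 7.2 plans for drop-outs, out-migration has its own form, and the stool collection forms ask why a specimen is missing; Form 2D lists refusal, absence and sickness. The incidence denominator in Section 7.2 also requires a person to be in the cohort at the end of two consecutive years, which can only reduce the count.

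What is at stake is whether the tabulated powers can be relied on for a village that just meets the cohort rule. The row with the smallest assumed effect has almost no slack, because its Year 2 power is 80.3%.

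**Working it through.** **1. Which survey is Year 1?** Section 7.2 indexes its incidence measures by K = 2 to 5, which makes Year 1 the baseline. Section 7.3 gives Year 1 its own 1% test and a power that rises with the bovine effect and with the share of bovines treated. The mass treatment of bovines starts in Stage 2 (November 2004), after the October 2004 baseline, so Year 1 in Section 7.3 must be the first follow-up. The 20% loss therefore begins after the first follow-up.

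**2. Numbers tested.** Behind the table: 300 in Year 1 and 300 × 0.8 = 240 in Year 2. From 300 enrolled with first-year loss d: 300(1 − d) in Year 1 and 240(1 − d) in Year 2.

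- d = 5%: 285 and 228
- d = 10%: 270 and 216
- d = 20%: 240 and 192

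All three values of d are assumptions. 20% is the protocol's rate for the following interval.

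**3. Attempt to reproduce the table.** Effective size per arm is 4 × 300 / 1.5 = 800 in Year 1 and 4 × 240 / 1.5 = 640 in Year 2. For the lowest row the reduction is 0.60 × 0.70 = 42%. The control rate is not stated. Taking the village-selection prevalence of 10-15% as an assumed range, a two-sided comparison of two proportions gives:

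- Year 1 (1% level): 70.5-90.8%, stated 26.7%
- Year 2 (5% level): 79.6-93.8%, stated 80.3%

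No single control rate fitted both columns under any test tried. The cumulative column does not follow from the other two either: 1 − (1 − 0.267)(1 − 0.803) = 85.6%, against 89.5% stated. The effect of fewer people is therefore scaled from each stated power.

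**4. Scaling.** The standardised effect implied by a stated power is nc = z(power) + z(1 − α/2), assuming a two-sided test. For the 60%/70% row:

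- Year 1: −0.622 + 2.576 = 1.954
- Year 2: 0.852 + 1.960 = 2.812

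New power = Φ(nc × √r − z(1 − α/2)), where r is the ratio of new to old effective sample size. Two versions of r:

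- *Design effect held at 1.5:* r = 1 − d.
- *Intracluster correlation held:* ICC = (1.5 − 1)/(300 − 1) = 0.0017, and effective size m/(1 + (m − 1) × ICC) is 200 for m = 300, 171.5 for 240 and 145.5 for 192. At d = 20%, r = 171.5/200 = 0.857 in Year 1 and 145.5/171.5 = 0.849 in Year 2.

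At d = 20%:

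- Year 1, design effect held: Φ(1.954 × 0.894 − 2.576) = 20.4%
- Year 1, ICC held: Φ(1.954 × 0.926 − 2.576) = 22.2%
- Year 2, design effect held: Φ(2.812 × 0.894 − 1.960) = 71.1%
- Year 2, ICC held: Φ(2.812 × 0.921 − 1.960) = 73.6%

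**5. Results for the 60%/70% row** (design effect held / ICC held):

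| First-year loss | Year 1 power % (stated 26.7) | Year 2 power % (stated 80.3) |
| --- | --- | --- |
| 5% | 25.1 / 25.6 | 78.3 / 78.8 |
| 10% | 23.5 / 24.5 | 76.1 / 77.3 |
| 20% | 20.4 / 22.2 | 71.1 / 73.6 |

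Scaling from a one-sided t-test with 3 degrees of freedom (four pairs) gives much the same at 20% loss: 21.7-23.1% in Year 1 and 72.7-74.8% in Year 2.

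**6. All nine rows, Year 2, 20% first-year loss:**

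| Effect and % treated | Stated | Design effect held | ICC held |
| --- | --- | --- | --- |
| 60 & 70 | 80.3 | 71.1 | 73.6 |
| 60 & 80 | 88.7 | 80.9 | 83.2 |
| 60 & 90 | 94 | 88.2 | 89.9 |
| 70 & 70 | 90.1 | 82.8 | 84.9 |
| 70 & 80 | 95.5 | 90.5 | 92.0 |
| 70 & 90 | 98 | 94.8 | 95.9 |
| 80 & 70 | 95.7 | 90.8 | 92.3 |
| 80 & 80 | 98.4 | 95.6 | 96.6 |
| 80 & 90 | 99.4 | 97.9 | 98.5 |

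**The case against.** **300 is a floor.** The rule sets a minimum in villages of about 1000 people, so a larger cohort would remove the problem. A reader might infer that the tabulated power will not be achieved. The documents do not support that: they show only that it is not secured when a village enrols the minimum. This limit stands.

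**First-year loss may be small.** The cohort is drawn from people already surveyed at baseline, those expecting to migrate or not living there continuously are excluded, and late stools lead to new containers. The 20% belongs to the next interval. This stands too, and is why a range is given. Even so, 5% loss takes the lowest row below 80%.

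**The table note may already cover it.** The note on attrition is not confined to Year 2, and on Section 7.2's numbering the 20% would be the loss from enrolment to first follow-up. But Section 7.3 defines the target as the number tested, and its Year 1 can only be a follow-up year. What stands is that the two numberings conflict and the table cannot be reproduced, so the number behind the Year 1 column cannot be verified. The squared nc in Year 2 is 1.6 to 2.1 times that in Year 1 although fewer people are tested, so something undisclosed enters the table. The scaled powers are therefore approximate.

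**Only one row is affected materially.** Eight of nine rows keep Year 2 power above 80%. The row that does not assumes 70% of bovines treated, while Section 5.2 calls for full coverage.

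**Later years.** A reader might carry 20% loss forward to Year 4 and claim a contradiction there. The table states no power beyond Year 2 and no loss rate for later intervals, so that does not follow.

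**Conclusion.** The point holds as a mismatch between the net 300 in the power basis and the gross 300 in the enrolment rule. At the stated minimum, any loss or stool non-return before Year 1 puts power below the table.

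The effect is modest. In the 60%/70% row, Year 2 power drops by about 2 points at 5% loss and by 7 to 9 points at 20%; Year 1 power drops by about 4 to 6 points at 20%. No other row falls below 80% in Year 2.

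These sizes assume that exactly 300 are enrolled, that the loss rates are as shown, that the tests are two-sided at the stated levels, and that the stated powers are a valid starting point. The mismatch itself depends on none of the sizes.

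**What to change.** 1. In Section 7.3, state the expected loss and stool non-return between enrolment and the first follow-up, and say whether 300 means enrolled or tested.
2. Restate the power table for 300 enrolled. At 20% first-year loss this means 240 tested in Year 1 and 192 in Year 2.
3. Give the control infection rate and the test behind the table, so that it can be reproduced.
4. Use one year numbering in Sections 7.2 and 7.3.

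These changes cost only wording, but the stated powers become less favourable.

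An alternative is to keep the table and require 300 tested at the first follow-up, enrolling 300/(1 − d) per village: 316 at 5% loss, 334 at 10%, 375 at 20%. No new baseline survey is needed, because all residents are already asked for stools then. It is not free: each member is examined at the annual survey and again one month after mass treatment, with two stools and six slides each time. Enrolling 75 more people adds up to 75 × 2 = 150 examinations per village per year, or 300 stools and 900 slides.
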